### Interim analyses {21b}

Interim analyses will not be performed for this study.

### Methods for additional analyses (subgroup) {20b}

To determine the magnitude of the possible mediating processes (DLMO, satiety, physical activity, and/or energy intake) between the intervention and the outcomes, parallel multiple mediation analysis is used.

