**Methods:**

In this randomized controlled trial, 60 people with prediabetes or type 2 diabetes with > 1 h social jetlag will be recruited. The intervention consists of bright light therapy (5000 lx) emitted by Vitamine-L (Lumie, UK) for 30 min each morning, combined with the advice to follow sleep advance instructions and to wear bright light-dimming goggles every evening for a period of 3 weeks. The control group adheres to their regular sleep habits and conditions. The primary outcome is glycated hemoglobin (HbA1c) after 12 weeks comparing the intervention and control in an intention-to-treat analysis. Secondary outcomes at 3 and 12 weeks are (1) social jetlag; (2) insulin sensitivity, fasting blood glucose, glucose-lowering medication use, and frequency of perceived hypoglycemia; (3) metabolic outcomes, including body mass index (BMI), waist circumference, body fat percentage, and blood pressure; (4) mood, including depression, fatigue and anxiety (measured with questionnaires); and (5) quality of life measured using EQ5D questionnaire. To assess other factors that might play a role as possible mediators, we will measure (para)sympathetic nervous system activity assessed with ECGs and electrochemical skin conductance tests, sleep quality and sleep phase distribution assessed with a sleep measuring headband (ZMax), the Dim Light Melatonin Onset in saliva samples (in a subgroup) at 3 and 12 weeks, the feeling of satiety and satiation with a 10-cm visual analog scale (VAS), diet using a food frequency questionnaire, and physical activity using an accelerometer (ActiGraph).

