**Discussion:**

Social jetlag can contribute to poorer glycemic control and metabolic control in those with type 2 diabetes. With this intervention, we aim to reduce social jetlag and thereby improve glycemic and metabolic control. This could offer a way to improve overall population health and to reduce the disease burden of type 2 diabetes.

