### Trial design {8}

This study is a randomized controlled intervention study with two conditions. Stratified randomization allocates participants 1:1 to control or intervention conditions with equal distribution of sex, age, and social jetlag.

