### Participant timeline {13}

Figures 1 and 2 present a timeline of the enrollment, study visits, intervention period, and measurements taken. Participants are invited to the research center in the afternoon and informed consent is signed. Then participants will go home and will fill out VAS scales about satiety and satiation before and after having dinner. A subgroup (*n* = 15) will be asked to wear light-dimming goggles for one evening and collect six saliva samples for melatonin onset assessment. After that, all participants will wear an activity tracker (ActiGraph) at home during regular activities and a sleep monitoring headband (ZMax) at night for a period of 6 days and they will fill in a sleep diary during this period. During the second study day at baseline, anthropometrics and blood pressure will be measured and blood will be drawn to determine HbA1c levels as well as fasting insulin and glucose levels. Participants will also fill in a VAS scale on satiety and satiation and several questionnaires. After that, an ECG and electrochemical skin conductance test will be performed. At the end of the visit and after the participants receive breakfast, they will be randomly assigned to either the control or intervention group and they will receive information on the intervention program or control condition.

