### Methods in analysis to handle protocol non-adherence and any statistical methods to handle missing data {20c}

Missing data will be investigated for all variables and multiple imputation by predictive mean matching will be used to address missing data if the prevalence exceeds 5%. Ten imputation sets with 50 iterations will be performed and results will be gained from pooled estimates.

To assess the influence of non-adherence to the intervention, we will conduct per-protocol analyses (participants with at least 80% adherence according to the sleep diary, accelerometer, and light tracker scores).

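### The parallel mediation model includes melatonin onset, which is collected in only 15 of 60 participants, and omits social jetlag, the trial's own causal route

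*Protocol article*

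**What the plan says.** **The model.** Section {20b} states that for the "possible mediating processes (DLMO, satiety, physical activity, and/or energy intake) between the intervention and the outcomes, parallel multiple mediation analysis is used". DLMO stands first in a list whose other members are planned without any subgroup restriction.

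**Who has DLMO.** Participant timeline {13}: "A subgroup (*n* = 15) will be asked to wear light-dimming goggles for one evening and collect six saliva samples for melatonin onset assessment". The Methods part of the Abstract confirms that follow-up is restricted in the same way: "the Dim Light Melatonin Onset in saliva samples (in a subgroup) at 3 and 12 weeks". Possible confounders and mediators also ties the saliva sampling to a subgroup. The whole trial is larger: "60 people with prediabetes or type 2 diabetes with > 1 h social jetlag will be recruited".

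**Missing data.** Section {20c} says missingness will be examined for every variable and that "multiple imputation by predictive mean matching will be used to address missing data if the prevalence exceeds 5" per cent. It makes no exception for variables collected only in a subgroup.

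**The expected route.** The Discussion part of the Abstract says "we aim to reduce social jetlag and thereby improve glycemic and metabolic control", and the main Discussion repeats the idea. Social jetlag is a secondary outcome at 3 and 12 weeks, with no subgroup restriction. It is not in the {20b} mediator list.

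**The concern.** A parallel multiple mediator model estimates each indirect effect conditional on the other mediators, so each person in the outcome model needs a value for every mediator. The mediator list, the subgroup size and the imputation rule are each stated, and together they do not fit.

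An analyst who follows the text has two routes. Complete cases discard three quarters of the trial, including usable data on the other three mediators. Imputation lets a small set of observed DLMO values stand in for most of the sample. Either way, the estimates for the well-measured mediators are damaged by the one that is hardly measured.

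The omission of social jetlag adds to this. The trial's reasoning is that the intervention reduces social jetlag and that this improves glycaemic control. The listed analysis leaves out the mediator that this reasoning names.

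**Working it through.** **Plan's own figures first.** Sample size {14} uses a difference of 0.25% with SD 0.25, α = 0.05 (two-sided assumed) and power 90%. The normal formula 2(1.960 + 1.282)²(0.25/0.25)² = 21.0 rounds up to 22 per group. With the t distribution, 22 per group gives 89.97% power and 23 gives 91.25%, so the stated 23 reproduces. For 25% drop-out, 23/0.75 = 30.7, against the stated 30 per group, which is close enough for this purpose. The DLMO subgroup of 15 comes with no calculation, so there is nothing to reproduce for it.

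**Share without DLMO.** (60 − 15)/60 = 45/60 = 75%, before any drop-out. If the 25% drop-out also applies in the subgroup (an assumption), 15 × 0.75 = 11.25, so about 11 people have follow-up values, and 1 − 11.25/60 gives about 81% missing among those randomised.

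**Route 1, complete cases.** Residual degrees of freedom = n − number of parameters. Assume that the {20a} covariates (baseline outcome and diabetes medication, counted as one term) carry over. The outcome model then has an intercept, arm, 4 mediators and 2 covariates, which is 8 parameters.

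| n | 8 parameters | 6 parameters (no covariates) |
|---|---|---|
| 60 | 52 | 54 |
| 15 | 7 | 9 |
| 11 | 3 | 5 |

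**Route 2, imputation.** Predictive mean matching fills each gap with an observed value from a donor. At least 45 values would come from at most 15 donors, about 7 or 8 per arm if the subgroup happens to split evenly. An even split is not assured: "Stratified randomization allocates participants 1:1 to control or intervention conditions", with strata for sex, age and social jetlag, and subgroup membership is not among them.

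**Illustrative power.** The documents give no path sizes, so those below are assumptions. The simulation had 4 mediators and 2 covariates, near-equal arms and no direct effect, with only one mediator active. An indirect effect counted as detected when both paths reached two-sided p < 0.05. There were 3,000 runs per cell, so the Monte Carlo standard error is at most √(0.25/3000) = 0.9 percentage points.

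| Arm to mediator (SD) | Mediator to outcome | n = 60 | n = 45 | n = 15 | n = 11 |
|---|---|---|---|---|---|
| 0.5 | 0.39 | 37% | 23% | 2% | 0.9% |
| 0.8 | 0.39 | 67% | 46% | 5% | 1.5% |
| 0.8 | 0.59 | 84% | 68% | 8% | 2.5% |
| 1.0 | 0.59 | 96% | 84% | 12% | 3.8% |

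The n = 45 column is what 25% drop-out leaves of 60. Across this range, power at n = 15 never exceeds 12%.

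**The case against.** **The wording leaves room.** Section {20b} speaks of possible processes, joins the list with and/or, and carries the word subgroup in its heading. A condensed article may also leave the choice of model and analysis set to the SAP. The latitude is real. But nothing says that DLMO is modelled separately, and if the heading did confine the analysis to the DLMO subgroup, that would be the 15-person case. The point concerns elements that the article does fix and that conflict with each other.

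**Values never scheduled are not missing data.** This is a fair reading of {20c}, and no sentence says that DLMO will be imputed for people who were never sampled. The rule for all variables permits imputation without requiring it. If it is not applied, the complete-case route remains.

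**The analysis cannot be run at all.** A reader might infer this, but the figures do not support it. On the 8-parameter count, 7 residual degrees of freedom remain at n = 15 and 3 at n = 11. The count goes negative only if four baseline mediator values are added at n = 11 (11 − 12 = −1), and {20b} does not specify those terms. Uninformative is the right word.

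**Social jetlag goes untested.** A reader might infer this too, and it is too strong. The effect of the intervention on social jetlag is a planned secondary comparison, and the Abstract presents the mediators as other factors. What is absent is the indirect effect on glycaemic outcomes through social jetlag.

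**It is only an additional analysis.** This stands, and it limits the weight of the point. Mediation is not a primary or secondary objective under Objectives {7}, although the Abstract includes possible mediators in the aim.

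**Conclusion.** The point holds. DLMO is absent by design in 75% of participants, yet it sits in a joint model with mediators planned for everyone. Followed as written, the model rests on at most 15 people (about 11 if drop-out is shared) or on at least 45 imputed DLMO values from at most 15 donors. The 75% and the 15 come straight from the article. The residual degrees of freedom of 7 and 3 assume that the {20a} covariates carry over, and the power ranges rest on assumed path sizes and only illustrate the loss. The conclusion does not depend on any one of those power figures.

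The mediator list also leaves the trial's stated causal route without an indirect-effect estimate.

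The point is worth correcting, but it does not threaten the trial's main result. The primary HbA1c comparison, the sample size and the secondary comparisons do not use this model.

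**What to change.** Amend {20b} and {20c} as follows:

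- Run the parallel mediation model in all randomised participants, using only mediators measured in everyone.
- Add social jetlag to the mediator list.
- For HbA1c at week 12, use week-3 mediator values where they are collected, so that the mediator precedes the outcome. Activity tracking is described for everyone after the 3-week period. The text does not expressly place the food frequency questionnaire at week 3, so its timing should be confirmed against the assessment schedule (Fig. 2, not shown here).
- Exclude DLMO from that model and from whole-sample imputation, stating that it is absent by design outside the subgroup.
- Report DLMO by arm in the subgroup, with confidence intervals, as a separate exploratory analysis.

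**Cost.** This changes analysis wording only and needs no new data. The price is that DLMO is no longer a formally tested mediator in the joint model. With 15 people, little information is given up.

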### Methods in analysis to handle protocol non-adherence and any statistical methods to handle missing data {20c}

Missing data will be investigated for all variables and multiple imputation by predictive mean matching will be used to address missing data if the prevalence exceeds 5%. Ten imputation sets with 50 iterations will be performed and results will be gained from pooled estimates.

To assess the influence of non-adherence to the intervention, we will conduct per-protocol analyses (participants with at least 80% adherence according to the sleep diary, accelerometer, and light tracker scores).

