### Sample size {14}

We calculated the sample size based on the primary outcome, namely HbA1c after 12 weeks. To date, no previous study investigating these social jetlag-reducing interventions has assessed metabolic outcomes. Previous lifestyle interventions in the target population show a change in HbA1c over a period of 3–6 months of 0.2–0.75% [19, 20]. We hypothesize a difference of − 0.25% in HbA1c levels between the two groups after the current intervention. To assess a change of − 0.25% ± 0.25 in HbA1c level, with an *α* of 0.05 and *β* of 0.1 the (corrected) number of participants needed is 23 persons per group, with an anticipated 25% drop-out, this results in 30 participants per group [19, 20].

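### Ten imputation sets are valid but few for the drop-out allowed for; 50 to 100 would make a near-threshold primary p-value more stable at almost no cost (minor)

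*Protocol article*

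**What the plan says.** The missing-data section {20c} states that "multiple imputation by predictive mean matching will be used to address missing data if the prevalence exceeds 5" per cent, and then sets the size of the procedure: "Ten imputation sets with 50 iterations will be performed and results will be gained from pooled estimates". It gives no reason for choosing ten.

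The sample size section {14} plans for missing outcomes well above that trigger: "with an anticipated 25% drop-out, this results in 30 participants per group". The statistical methods section {20a} specifies an intention-to-treat linear regression adjusted for baseline. The primary outcome {12} is HbA1c at 12 weeks. If drop-out is near the planned figure, the primary result will therefore be a pooled estimate from ten imputed data sets.

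**The concern.** Multiple imputation draws random values, so its pooled estimate and p-value carry Monte Carlo error that depends on the seed. This error shrinks as the number of sets m grows. With a quarter of 60 outcomes possibly missing, ten sets leave a visible amount. Two analysts following the same plan on the same data could report noticeably different p-values. Near 0.05 they could differ on whether the primary result is significant. This error can be reduced without adding any data, and the article itself fixes the number that controls it.

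**Working it through.** **Inputs from the article.** m = 10 {20c}; 60 participants, 30 per group, 25% drop-out {14}; 1:1 allocation {8}; baseline-adjusted regression {20a}; planned difference 0.25% HbA1c. The 0.25 after the ± sign in {14} is read as the SD, so the planned effect is 0.25/0.25 = 1 SD.

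**Inputs assumed.** Outcomes missing at random or completely at random, only the outcome missing, 5 donors for predictive mean matching, and a baseline–outcome correlation of 0, 0.5 or 0.8. The article gives none of these.

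**1. The plan's own figure.** Normal approximation, two-sided 0.05, power 0.90: 2 × (1.96 + 1.2816)² × (0.25/0.25)² = 21.01, so 22 per group. The exact t-test gives power 0.8997 with 22 and 0.9125 with 23, which reproduces the stated 23. Allowing for drop-out, 23/0.75 = 30.67 against the stated 30; the difference is immaterial here. Expected missing outcomes: 0.25 × 60 = 15.

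**2. Efficiency.** Relative efficiency is 1/(1 + FMI/m), where FMI is the fraction of missing information. With FMI = 0.25 it is 0.976 at m = 10, 0.995 at m = 50 and 0.9975 at m = 100. The average loss with ten sets is about 2%.

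**3. Seed-to-seed movement of the estimate.** In units of its standard error this is about √(FMI/m). With FMI = 0.24:

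- m = 10: √0.024 = 0.155
- m = 50: √0.0048 = 0.069
- m = 100: √0.0024 = 0.049

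Simulation at m = 10 gave 0.152.

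**4. Hand check on the p-value scale.** Take z = 1.96 (p = 0.05). A 95% seed range of ±1.96 × 0.155 = ±0.304 moves z between 1.656 and 2.264, so p runs from about 0.098 to 0.024. The simulated range is somewhat wider, because the pooled standard error and degrees of freedom also vary.

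**5. Simulation near the threshold** (60 participants, 15 outcomes missing, Rubin pooling with small-sample degrees of freedom; the converged p comes from thousands of imputations):

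| Quantity | m = 10 | m = 50 | m = 100 |
|---|---|---|---|
| Converged p 0.045–0.055: 95% seed range of p | 0.02–0.12 | 0.034–0.074 | 0.038–0.065 |
| Converged p 0.035–0.045: chance that a run gives p ≥ 0.05 | 38–39% | 16–17% | 9% |
| Converged p 0.025–0.035: chance that a run gives p ≥ 0.05 | 17–19% | 1% | 0% |
| Converged p 0.02–0.10: chance of the other side of 0.05 | 21–25% | 8–9% | 6% |

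The first three rows were nearly the same for baseline correlations of 0.5 and 0.8.

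**6. The same chance over all data sets, not only those near 0.05, at m = 10:**

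- No effect: about 1.5%.
- Planned 1 SD effect: 3.9%, 1.7% and about 0% for baseline correlations of 0, 0.5 and 0.8.
- Half the planned effect: about 5 to 6%, against about 2 to 2.5% at m = 50 and 2% or less at m = 100.
- With 10% missing instead of 25%: about 1% under no effect and 0 to 1.1% under the planned effect.

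The absolute gain from 50 sets is roughly 0 to 3.5 percentage points.

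**7. With a strong auxiliary variable** in the imputation model (assumed; FMI about 0.11), the chance of p ≥ 0.05 for a converged p of 0.035–0.045 is 27%, 9% and 4% at m = 10, 50 and 100. The pattern is the same but smaller.

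**The case against.** Ten sets are not an error. They give valid, unbiased inference at 98% efficiency, and nothing in {20c} is miscalculated or contradicts another section. The one-in-five figure applies only to results already near 0.05; over all results the chance is a few per cent at most. The 25% is a planning allowance, and the retention section {18b} notes that participants come from cohorts already used to research, so actual missingness may be lower. More sets do not remove the problem either. If the converged p is almost exactly 0.05, the seed decides the side at any m, and reading the estimate with its interval is the better safeguard. All of this stands, and it limits the point to a minor one.

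It does not remove the point. Efficiency describes average precision, not whether a reported p-value repeats. A recorded seed makes one draw repeatable but no less arbitrary.

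A reader might also infer more than the article supports:

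- That the primary analysis is invalid or biased. It is not.
- That the trial has a one-in-five chance of reversing its conclusion. That figure holds only for a converged p of 0.02–0.10.
- That 50 iterations is wrong. Nothing here shows that.
- That a missing seed or an unlisted imputation model is an omission. Both are ordinary content of an analysis plan, which is not shown.

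**Conclusion.** The point holds as a minor improvement that is practically free. Ten sets at the planned drop-out leave a seed-to-seed movement of about 0.15 SE in the primary estimate, against about 0.07 with 50 sets and 0.05 with 100. This matters only when p is near 0.05 and missingness is near 25%: about one run in five then crosses the threshold, falling to 6 to 9% with more sets. Unconditionally the chance is about 1 to 2% under no effect or the planned effect (about 4% if baseline is uncorrelated with outcome) and about 6% at half that effect. With 50 to 100 sets it is about 2% or a little above in the worst case examined. These figures rest on the assumed missingness mechanism, correlations and donor number, on drop-outs lacking week-12 HbA1c, and on reading ±0.25 as an SD. With less missing data they shrink.

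**What to change.** In {20c}, change the number of imputation sets for the primary analysis from ten to at least 50, preferably 100. The iterations can stay as they are.

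Two additions are optional and may already be in the analysis plan: a seed recorded in advance, and week-3 HbA1c as an auxiliary variable in the imputation model. The participant timeline {13} repeats the baseline blood draw at 3 weeks, so that value should exist for anyone who attends.

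The cost is one line of wording and seconds to minutes of computing for 60 records. No participants, visits or measurements are added. The article reports the trial as ongoing, so the change could be made before the analysis.

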### Plans to give access to the full protocol, participant-level data and statistical code {31c}

After finalization and publication of the study, access to the protocol and statistical code can be requested.

### Composition of the data monitoring committee {21a}

There is no data safety monitoring board (DSMB) or safety committee established for this study given its low-risk profile. On-site monitoring of the study site will be performed regularly by an independent monitor of the Clinical Monitoring Center (CMC) of the Amsterdam UMC.

### Adverse event reporting and harms {22}

Given the noninvasive nature of the study procedures and intervention, we do not expect any serious adverse reactions. Furthermore, events reported spontaneously by participants or observed by the investigator that have a prolonged effect on the physical wellbeing of the participant (e.g., sustained injury caused by a conducted study measurement or sustained injury incurred during the study visit but unrelated to the study measurements) will be reported. Adverse events will be reported to the local ethical committee in the annual progress report.

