### Intervention description {11a}

The intervention condition is a combination of evidence-based techniques to realign social jetlag. It consists of three components: bright light therapy in the morning, sleep advance instructions, and bright light reduction in the evening.

First, for the bright light therapy, a Vitamin-L lamp (Lumie, UK) will be placed at 30 cm before the participant, yielding 5000 lx (https://www.lumie.com/products/vitamin-l), which is similar to outside light levels on a clouded day. The participant does not have to look straight into the light. Participants are requested to expose themselves to 30 min of bright light each morning by sitting in front of the lamp, while working on their computer or reading. Participants will receive a Vitamin-L lamp together with instructions for use. The Vitamin-L lamp is certified to ISO 13485 Medical Devices, QMS standard. Lights must pass rigorous safety tests and be supported by clinical research to meet the Medical Devices Directive EC93/42/EEC. They are approved for use for light therapy at home. Thus, in the present protocol, the lights will be used for the purpose they are designed for (i.e., administration of light). Due to recent insights about possible interactions of different photoreceptors in the non-visual effects of light [14], we believe that it is probably most efficient to use full spectrum bright light in the morning, rather than select a certain specific wavelength, such as blue light only.

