Second, study participants are told to sleep more regularly, with similar sleep onset and sleep offset times on weekdays and weekend days. To support them with this, participants will follow a personal sleep-advancing scheme [8]. Based on self-report of the participant, the habitual sleep onset and habitual sleep offset will be calculated as the average of all days (week and weekend days). Then participants are asked to give their preferred sleep offset for all days of the week (similar for week and weekend days); preferred sleep onset is calculated as sleep offset − preferred sleep duration between 7 and 8 h. To advance sleep time with an average 20 min, the first 3 days, the light therapy will be scheduled 10 h after preferred sleep onset. On days 4–6, the light therapy is scheduled 9 h after preferred sleep onset and days 7–9 the light therapy 8 h after preferred sleep onset, if the earlier sleep onset is 3 h earlier. After the preferred sleep offset and onset are reached, the new schedule will be continued during the rest of the 3 weeks intervention.

As final part of the intervention, participants receive blue-light dimming goggles with instructions to wear them every evening from 18.00 h until they go to sleep [15]. When wearing the goggles they can still perform their usual activities, such as watching television or reading, with screens of electronic devices in dimmed modus [15, 16] as well as room lighting (dim lighting of the room, curtains closed).

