**Fig. 2 Fig2:**
[figure not shown]
Schedule of enrolment, interventions, and assessments social jetlag trial

To improve adherence to the protocol and assess compliance, 1 week after starting the intervention, participants will keep a sleep diary of 7 days and wear an accelerometer as well as a light tracker.

After a period of 3 weeks, all participants will wear an activity tracker and a sleep-monitoring headband for 5 days and fill in a sleep diary. After that, participants will be invited back to the research center once for the same measurements as the second day of the baseline visit (anthropometrics, blood pressure, blood draw, ECG and SUDO, and questionnaires). Twelve weeks after the start of the intervention, they will wear an activity tracker for 5 days again and they will come back to the research center for a final visit repeating the same measurements.

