Especially people with prediabetes or early-stage type 2 diabetes could benefit from this intervention to reduce their social jetlag. As these people are at high risk of developing or deteriorating in their diabetes, reducing the metabolic and glycemic burden could possibly help them reverse this disease progress and return to a healthy metabolic state. Additionally, given its exceptionally high prevalence of 50–70% in the general population, social jetlag is an important public health concern to tackle [2, 3]. Educating people at risk about the importance of regular sleep timing and the possibilities to reduce social jetlag to lower glycemic and metabolic burden could increase the implications of our study outcomes.

Strengths of our study design are the elaborate measurements of sleep timing and also repeated measurements of sleep quality using an EEG sensor headband that will provide in-depth insight into participants’ sleep quality. Additionally, we will follow up with participants 8 weeks after the intervention period for a final assessment of long-term glycemic control (HbA1c). Limitations of this study are the inability to use a double-blind study design due to the nature of the intervention. As the intervention is behavioral, the control group might also change their behavior somewhat, such as their sleep rhythms, physical activity, or dietary patterns. This may lead to a larger effect. However, this effect can also be expected in the intervention group and might be an additional working mechanism.

If this study shows that social jetlag can be reduced and metabolic and glycemic control can thereby be improved in people with prediabetes and type 2 diabetes, this may offer a new possibility for lifestyle interventions in this group.

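### Harms reporting is passive with a threshold of prolonged physical effect, so short-lived complaints from the lamp, goggles or sleep schedule cannot be compared reliably by arm

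*Protocol article*

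**What the plan says.** The protocol article deals with harms in one section, Adverse event reporting and harms {22}. It gives the expectation that "we do not expect any serious adverse reactions". It then says that reporting will cover "events reported spontaneously by participants or observed by the investigator that have a prolonged effect on the physical wellbeing of the participant". The examples in brackets are "sustained injury caused by a conducted study measurement or sustained injury incurred during the study visit but unrelated to the study measurements". The section ends: "Adverse events will be reported to the local ethical committee in the annual progress report".

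The exposure is described under Intervention description {11a}. On the lamp: "Participants are requested to expose themselves to 30 min of bright light each morning". Goggles are worn every evening from 18.00 h, and sleep is moved earlier in steps, after which "the new schedule will be continued during the rest of the 3 weeks intervention". All of this takes place at home and in the intervention arm only.

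Both arms attend the research centre after the intervention period and again at 12 weeks. On the first of these, Participant timeline {13} says that "participants will be invited back to the research center once for the same measurements as the second day of the baseline visit". Who will be blinded? {17a} states that neither participants nor the research team can be blinded.

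**The concern.** For a low-risk behavioural programme, the realistic safety question is everyday tolerability: headache, eye strain, or complaints while sleep is being shifted. Serious reactions are a lesser concern. The stated criterion suits this question poorly in two ways.

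First, an event has to be volunteered or noticed, and then has to be prolonged and physical. A headache that passes within hours meets neither the duration threshold nor, probably, the chance of being mentioned at a visit weeks later.

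Second, spontaneous reporting in an open-label trial depends on having something to attribute a complaint to. Intervention participants have a lamp, goggles and a schedule; controls have sleep-hygiene advice. The propensity to report can therefore differ by arm even if the complaint rate does not.

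The Discussion says of the programme, should it succeed, that "this may offer a new possibility for lifestyle interventions in this group". Anyone acting on that would want to know how well it was tolerated, and a short list of spontaneous reports would not tell them.

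**Working it through.** **1. Denominators.** The article's only figures that bear on precision are its sample sizes (Sample size {14}): difference 0.25, SD 0.25, alpha 0.05 (taken as two-sided), power 0.90.

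- Normal approximation: n = 2 × (1.960 + 1.282)² × (0.25/0.25)² = 21.01, so 22 per arm.
- Noncentral t: power is 0.8997 at 22 and 0.912 at 23, which gives the stated 23.
- Drop-out of 25%: 22/0.75 = 29.3, so 30; 23/0.75 = 30.7, so 31. The stated 30 is within rounding of these.

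I use 30 per arm (all randomised) and 23 per arm (after the anticipated drop-out).

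**2. What zero events would show with complete capture.** One-sided 95% upper bound = 1 − 0.05^(1/n).

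- n = 30: 9.5%
- n = 23: 12.2%

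**3. What zero reports would show with incomplete capture.** The article gives neither a complaint rate nor a capture rate, so both are assumed here. Take a true rate of 20% for a transient complaint and a probability c that it reaches the record. Then P(none of 30 seen) = (1 − 0.20c)^30.

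| Capture c | Effective rate | P(none of 30) |
|---|---|---|
| 100% | 0.20 | 0.001 |
| 50% | 0.10 | 0.04 |
| 25% | 0.05 | 0.21 |
| 10% | 0.02 | 0.55 |

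With full capture, silence would be strong evidence against a 20% rate. With low capture it is close to uninformative.

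**4. What is already collected in both arms.**

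| Possible effect | Systematic measure in both arms | Section |
|---|---|---|
| Hypoglycaemia | Questionnaire, 3 and 12 weeks | Secondary outcomes |
| Fatigue, mood, depression, anxiety | Questionnaires, 3 and 12 weeks | Abstract; Secondary outcomes |
| Disturbed sleep | Headband, activity tracker and diary after 3 weeks | Participant timeline {13} |
| Headache, eye strain, discomfort with lamp or goggles | None stated | – |

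The gap is the last row.

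**5. What solicited collection could deliver.** Power to detect 10% v 30% is 0.49 with 30 per arm and 0.39 with 23. For 5% v 30% it is 0.73 and 0.61. This supports a descriptive comparison, not a test.

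**The case against.** The strongest reply is that the harms section can be read as a rule on what is forwarded. It says that certain events will be reported; it does not say that nothing else is recorded, and its closing sentence on the ethics committee mentions adverse events without any threshold. A reader might infer that short-lived complaints are never recorded. The article does not say so. Nor do the examples restrict the rule to study visits: they are introduced as examples, and a prolonged physical effect of the lamp at home would qualify.

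A reader might also infer that the arms cannot be compared on harms at all. That is not supported either: perceived hypoglycaemia, fatigue, mood, anxiety and sleep are measured in both arms and include plausible effects of a sleep advance.

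It can further be said that event forms and harms tables belong in the full protocol or analysis plan, which are not shown. That holds for their absence from the article, and I make no point of it. It does not dispose of the criterion that the article does state: spontaneous or observed, prolonged, physical.

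Three further objections stand in part. The 20% rate and the capture rates are assumptions. Solicited answers remain unblinded, so asking everyone the same question reduces differential reporting without removing it. A change during the trial mixes two methods of ascertainment, which the tabulation has to show.

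**Conclusion.** The point holds as a limited one and is a cheap improvement, not a flaw that threatens the primary analysis. The stated criterion is passive and tied to prolonged physical effects, and no solicited collection of short-lived complaints about the lamp, goggles or schedule is stated. With open-label allocation and devices in one arm only, adverse events outside the existing questionnaire and sleep measures cannot be compared reliably by arm, and a low count of reports would not establish good tolerability.

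The size depends on assumptions. The bounds of 9.5% (n = 30) and 12.2% (n = 23) need only complete capture. The 55% to 21% chance of seeing no event rests on an assumed 20% complaint rate and 10% to 25% capture, and only illustrates how little silence would mean.

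**What to change.** At the existing 3- and 12-week visits, ask both arms, in identical words, one open question about new complaints since the last visit, followed by a short fixed checklist (for example headache and eye strain). Record every event regardless of duration. Tabulate descriptively by arm, with participants enrolled before and after the change shown separately. Keep the present threshold only for what is forwarded to the ethics committee, and say in the text that this is its purpose.

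The cost is one short eCRF form, a minor amendment and slightly more data entry, with no extra visits or staff. Trial status gives a start in April 2024 and recruitment expected to be complete in 2025, so participants who have already finished will have no solicited data. Power stays limited at 23 to 30 per arm, so the table should be presented as description, with confidence intervals, and not as a test of safety.
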